The number of patients enrolled per site and per period will vary. Under the current circumstances, a short "wash-out" period of at least 1 day is planned, allowing the removal of the equipment necessary for the intervention for the centers having started with the intervention.

The total duration of the study will be 2 months and 30 days maximum (+ wash-out) per center + patient follow-up over a period of 15 days  $\pm$  10.

Once regulatory authorisations have been obtained, the sites will be set up (January 2021), then the actual start-up of the 18 sites will be spread out over a period of about 30 days for feasibility reasons.

Due to the experimental design and the type of intervention, the trial will be conducted as open-label to participants and caregivers. The risk of bias related to the evaluation of the primary outcome in an open-label trial is here limited due to its objective nature (i.e., new infection diagnosed SARS-CoV-2+).

The DEPIST-COVID study will be conducted prior to the ANRS DEPIST trial, the start of which was initially planned for October 2020.

The ANRS DEPIST trial is a randomised, stepped-wedge trial and concerns the evaluation of a nurse-led HIV testing strategy in 18 emergency departments in the Paris Metropolitan area which will, for the most part, be the sites participating in the DEPIST-COVID study, which facilitates its implementation. The DEPIST trial obtained regulatory authorisations. The Coordinating Investigator ([name]) conducted a study start-up meeting at the 18 sites with the head of the department, the medical contacts and the nursing contacts in July 2020. Regulatory implementation meetings were underway in September 2020.

[figure not shown]

La période 1 correspond à la période Pratique actuelle ;  
la période 2 à la période Dépistage SARS-CoV2 systématique + Pratique actuelle.  
Les couleurs denses correspondent aux échéances des livrables

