##### Secondary endpoints analyses

- The proportion of patients tested positive for SARS-CoV-2 among the asymptomatic or paucisymptomatic patients tested by nurses and that in the Paris Metropolitan area at the same period will be compared using an asymptotic Wald test.  
The proportion obtained in each emergency department will be compared to that of the department's IRIS geographical area using an asymptotic Wald test. The same comparisons will be made across the entire tested population.
- The feasibility of the testing will be described: proportion of patients who have completed the questionnaire, proportion of offered, accepted and performed tests, and notified of the SARS-CoV-2 result and staff involved (nurses, caregivers, doctors, others),
- The proportion of patients tested positive for SARS-CoV-2 among the patients tested by nurses, the proportion of asymptomatic patients among the patients tested by nurses and the proportion of asymptomatic patients among the patients tested positive for SARS-CoV-2 will be described.

|                        |              |
|------------------------|--------------|
| Study                  | DEPIST-COVID |
| Promotion/gestion code | APHP201625   |
| Study coordinator      | [name]   |

- The symptoms of patients tested positive for SARS-CoV-2 will be described in the patients completed the questionnaire.
- Exposure factors will be described using the items in the DEPIST-COVID questionnaire. Among patients tested, the exposure factors associated with the positivity of the SARS-CoV-2 test will be analysed using a generalised linear mixed model (binomial distribution or other distribution adapted to the data). The exposure factors will be considered as fixed effects and the site as a random intercept. Other fixed variables could be added to the model if appropriate.
- The sociodemographic, behavioural and practical factors of diagnosed patients associated with positive SARS-CoV-2 infection will be described for the schemes (DEPIST-COVID, ComCor) according to the types of variables (proportion, mean and standard deviation or median, Q1-Q3) and presented with their 95% confidence interval. If appropriate, the factors will also be analysed in the population of DEPIST-COVID cases (positive tested patients) and controls (negative and matched tested patients).

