## Changes to the analysis plan

### **Primary endpoint analysis**

The primary outcome will be analysed using a generalised linear mixed model (Poisson distribution or any other distribution adapted to the data) with the centre as a random intercept, the centre-by-period interaction as random effect and the strategy, the period and the incidence rate-by-period interaction as fixed effects. The logarithm of the number of patients will be included as an offset term in the model.

The period will be modelled as weekly (1 to 15).

Patients considered non-positive for SARS-CoV-2 will be patients not tested, patients tested negative or with an undeterminate result and patients tested positive with a known SARS-CoV2+ status for less than 3 months.

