### **Secondary endpoints analyses**

- Factors associated with performing systematic nurse-driven screening will be analysed in patients who had screening offer using a generalised linear mixed model (binomial distribution) with the centre as a random intercept and the patient characteristics as fixed effects.

- The factors associated with new SARS-CoV-2 diagnoses will be analysed using a generalised linear mixed model (binomial distribution) with the centre as a random intercept and patient characteristics as fixed effects.

- The proportions of new SARS-CoV-2 diagnoses through systematic nurse-driven screening overall and per ED, and proportion among all patients tested in EDs, will be compared to the proportion of positive tests among adults tested in the geographical departments of the Paris Metropolitan area using the Miettinen-Nurminen method for risk difference and 95% CI estimations.

[figure not shown]

Coller ici l'étiquette patient

N° DOSSIER :

\_\_\_\_\_  
Centre

\_\_\_\_\_  
Patient

PLEASE FILL OUT THIS QUESTIONNAIRE BY CHECKING THE SQUARE  
CORRESPONDING TO YOUR RESPONSE [figure not shown]

1 You are:

☐ male ☐ female

2 What is your date of birth?

Month Year

3 Do you have symptoms suggestive of Covid-19?

☐ Yes ☐ No

> If yes, please precise:

☐ Fever (>38°C)  
or fever sensation

☐ Cough

☐ Loss of smell

☐ Muscular pain

☐ Unusual fatigue

☐ Breathing difficulty  
(shortness of breath)

☐ Loss of taste

☐ Other

☐ Headache

☐ Sore throat

☐ Diarrhoea

☐ Runny nose

> If yes, date of first symptoms:

Day Month Year

4 What is your postcode?

5 In which country were you born?

☐ France

☐ Other

Please specify your country of birth:

6 Until what age did you study?

years

7 Currently (over the last month):

☐ You work

☐ You do not work

☐ You are seeking employment

☐ You are a student

> If you work:

• Do you work away from home?:

☐ Yes

☐ No

☐ Partially

• Does your occupation expose you to contacts with:

- Members of the public?

☐ Yes

☐ No

- Sick persons?

☐ Yes

☐ No

8 What is your medical coverage:

☐ Social security without supplementary health insurance

☐ CMU (Universal medical cover)

☐ Social security with supplementary health insurance

☐ AME (State medical assistance)

☐ No medical coverage

☐ Other

9 Do you suffer from a chronic disease (diabetes, high blood pressure, angina pectoris, chronic bronchitis, asthma or chronic respiratory disease)?

☐ Yes

☐ No

10 Do you currently smoke cigarettes?

☐ Yes

☐ No

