# Appendix C. Table Emergency department characteristics and study period duration

Table C1. Emergency department characteristics and study period duration

| ED center                                                     | 1     | 2     | 3     | 4     | 5     | 6     | 7     | 8     | 9     | 10    | 11    | 12    | 13    | 14    | 15    | 16    | 17    | 18    |
|---------------------------------------------------------------|-------|-------|-------|-------|-------|-------|-------|-------|-------|-------|-------|-------|-------|-------|-------|-------|-------|-------|
| Pediatric care                                                | 0     | 0     | 0     | 0     | 1     | 0     | 1     | 0     | 1     | 0     | 1     | 1     | 0     | 0     | 0     | 1     | 0     | 0     |
| University hospital                                           | 1     | 1     | 1     | 1     | 0     | 1     | 1     | 1     | 0     | 1     | 1     | 1     | 1     | 1     | 0     | 1     | 0     | 1     |
| Inner Paris ED                                                | 1     | 1     | 1     | 0     | 0     | 0     | 0     | 1     | 0     | 0     | 0     | 0     | 1     | 1     | 0     | 0     | 1     | 1     |
| Annual patient admissions in 2021 a                | 74654 | 50891 | 57430 | 43990 | 91752 | 39977 | 96287 | 76855 | 53692 | 33083 | 59663 | 68957 | 58560 | 34630 | 26183 | 57635 | 62700 | 47550 |
| SARS-CoV-2 device for rapid testing in routine care in the ED | 1     | 1     | 1     | 1     | 0     | 1     | 0     | 1     | 0     | 0     | 0     | 0     | 1     | 1     | 0     | 0     | 1     | 0     |
| Control study period (days) b                      | 37    | 33    | 26    | 34    | 35    | 35    | 36    | 29    | 40    | 30    | 32    | 30    | 31    | 40    | 40    | 35    | 35    | 25    |
| Intervention study period (days) b                 | 37    | 33    | 26    | 34    | 35    | 35    | 36    | 29    | 38    | 30    | 32    | 30    | 31    | 40    | 40    | 35    | 35    | 30    |
| Wash-out study period (days) b                     | 1     | 2     | 1     | 1     | 2     | 1     | 2     | 1     | 2     | 1     | 2     | 1     | 2     | 1     | 1     | 2     | 7     | 2     |

Data are presented as numbers or No 0/Yes 1.

ED: Emergency department.

aAnnual patient admissions included pediatric admissions.

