| Hospitalization                                                                              | .                            | 24 (1.8)                       | .                                    | 2 (5.6)                     | .                                       | 22 (1.7)                    | 3.9 (-0.3, 16.5)            |
| Only emergency department visit: outpatients                                                 | .                            | 1304 (98.2)                    | .                                    | 34 (94.4)                   | .                                       | 1270 (98.3)                 | -3.9 (-16.5, 0.3)           |
| Among patients with rapid multiplex respiratory virus test, other respiratory viruses | 581                          | .                              | 116                                  | .                           | 465                                     | .                           | .                           |
| Yes*****                                                                                     | .                            | 77 (13.3)                      | .                                    | 5 (4.3)                     | .                                       | 72 (15.5)                   | -11.2 (-15.7, -5.2)         |

\* Patients with indeterminate results or a known positive SARS-CoV-2 status were not included in this table. In univariate analysis, factors associated with new infections diagnosed through screening for asymptomatic/paucisymptomatic patients were mainly older age, having mild symptoms, not being from France, particularly being from Sub-Saharan Africa, being unemployed, not having medical coverage, living in a community, being a case contact and not being previously screened.

\*\* Among patients who underwent a rapid molecular SARS-CoV-2 test, 258 (7.4%) reported having symptoms. Among patients who underwent a rapid multiplex respiratory virus test, 508 (90.1%) reported having symptoms.

\*\*\* Chronic diseases: diabetes, arterial hypertension, angina pectoris, chronic bronchitis, asthma or chronic respiratory disease

\*\*\*\* For this variable of the DEPIST-COVID questionnaire, data were collected in 8 centers, and it was not possible to collect them later in the remaining 10 centers. Findings are presented for 8 centers (n=1,510 patients, missing data: 12.1% in the 8 centers).

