#### Reference

Appendix J. Comparison of the proportions of new SARS-CoV-2 diagnoses through screening in emergency departments and of positive tests through community screening for individuals aged 18+ of the geographical departments of the Paris metropolitan area screened during the same period

- a. Table J1. New SARS-CoV-2 infections diagnosed through screening in emergency departments for asymptomatic/paucisymptomatic patients and positive tests through community screening for asymptomatic adults in the geographical departments of the Paris metropolitan area during the same period

| SARS-CoV-2 positive tests | Total population |                | SARS-CoV-2 screening for asymptomatic / paucisymptomatic patients in EDs |             | Community screening for SARS-CoV-2 in the Paris metropolitan area* |                | Risk difference (95% Confidence interval) |
|---------------------------|------------------|----------------|--------------------------------------------------------------------------|-------------|--------------------------------------------------------------------|----------------|-------------------------------------------|
|                           | N                | n (%)          | n                                                                        | n (%)       | n                                                                  | n (%)          |                                           |
|                           | 3404867          | .              | 4283                                                                     | .           | 3400584                                                            | .              | .                                         |
| Yes                       | .                | 156522 (4.6)   | .                                                                        | 224 (5.2)   | .                                                                  | 156298 (4.6)   | 0.6 (0.01, 1.3)                           |

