| No                        | .                | 3248345 (95.4) | .                                                                        | 4059 (94.8) | .                                                                  | 3244286 (95.4) | -0.6 (-1.3, -0.01)                        |

\* Source: Community screening data were provided by Santé publique France on May 20, 2022.

- b. Table J2. New SARS-CoV-2 infections diagnosed through screening in emergency departments (EDs) for asymptomatic/paucisymptomatic patients per ED and positive tests through community screening for asymptomatic adults tested in the corresponding geographical department

| SARS-CoV-2 positive tests | Total population |             | SARS-CoV-2 screening for asymptomatic / paucisymptomatic patients in EDs |          | Community screening for SARS-CoV-2 in the geographical department* |             | Risk difference (95% Confidence interval) |
|---------------------------|------------------|-------------|--------------------------------------------------------------------------|----------|--------------------------------------------------------------------|-------------|-------------------------------------------|
|                           | N                | n (%)       | n                                                                        | n (%)    | n                                                                  | n (%)       |                                           |
| Center 1                  | 453511           |             | 429                                                                      |          | 453082                                                             |             |                                           |
|                           |                  | 15782 (3.5) |                                                                          | 23 (5.4) |                                                                    | 15759 (3.5) | 1.9 (0.1, 4.4)                     |
| Center 2                  | 414301           |             | 357                                                                      |          | 413944                                                             |             |                                           |

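### The pooled ED-versus-community comparison (Table J1) is not weighted to where and when the EDs screened; standardised to Table J2, the excess is 0.52 rather than 0.63 points and its interval includes zero

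*Combined protocol and SAP*

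**What the plan says.** Protocol section 2.2 states the hypothesis: positivity among asymptomatic ED patients is compared with that of the region, and is expected to be higher in the ED.

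Section 1.1 of the final SAP says that the ED proportion and "that in the Paris Metropolitan area at the same period will be compared using an asymptotic Wald test". The later page headed Changes to the analysis plan replaces that method. It plans overall and per-ED comparisons with adults tested in the departments of the region, "using the Miettinen-Nurminen method for risk difference and 95% CI estimations". Neither text says how the overall comparison is aligned by ED, date or department.

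Table J1 is the overall comparison, against "positive tests through community screening for asymptomatic adults in the geographical departments of the Paris metropolitan area during the same period". It reports 0.6 (0.01, 1.3) points. Table J2 is the per-ED comparison, against "positive tests through community screening for asymptomatic adults tested in the corresponding geographical department". Its caption names no period. The title of Appendix J repeats the same-period label without dates.

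The EDs did not share one screening period. Under protocol section 5.1, "the actual start-up of the 18 sites will be spread out over a period of about 30 days", and the order of the two strategies was randomised. Table C1 gives intervention periods of 26 to 40 days, and the primary model numbers the weeks 1 to 15.

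**The concern.** A single regional pool is weighted by the volume of community testing. The ED group is weighted by how many patients each ED screened in its own weeks. These weights differ, and community positivity in Table J2 runs from 2.0% to 8.4%, so the difference in mix can move the estimate. This concerns the point estimate, apart from how wide the interval should be.

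Table J1 is the only pooled asymptomatic/paucisymptomatic comparison bearing on the hypothesis in section 2.2; Table J3 covers all tested patients. Its lower limit clears zero by less than 0.01 points, so even a small shift changes what can be said.

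**Working it through.** **1. Reproduce Table J1.** 224/4,283 = 5.230%; 156,298/3,400,584 = 4.596%; difference 0.634 points. The Miettinen-Nurminen 95% interval is 0.006 to 1.342, which rounds to the printed 0.6 (0.01, 1.3). A Wald interval on the same data has SE = sqrt[p1(1 - p1)/n1 + p2(1 - p2)/n2] = 0.340 points and runs from -0.03 to 1.30.

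**2. Is Table J1 the sum of Table J2?** The ED columns of Table J2 sum exactly to Table J1 (224 and 4,283). The community tests in Table J2 sum to 5,451,969, not 3,400,584. The two tables use differently built comparators.

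**3. What window does Table J2 use?** The eight inner-Paris EDs (centres 1, 2, 3, 8, 13, 14, 17, 18) have eight different community counts, from 346,255 to 507,782. Divided by the intervention days in Table C1, they give 12,245 tests per day (centre 1: 453,082/37) to 14,663 (centre 13: 454,558/31). That narrow range suggests that each count was cut to the ED's own intervention period. It is an inference: control and intervention lengths are equal in 16 of 18 EDs, so the counts alone cannot fix the dates.

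**4. Standardise to Table J2.** Expected positives per ED = number screened x community positives/community tests.

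| Centre | Screened | Positive | Community % | Expected |
|---|---|---|---|---|
| 1 | 429 | 23 | 3.48 | 14.92 |
| 2 | 357 | 10 | 3.57 | 12.74 |
| 3 | 129 | 2 | 3.70 | 4.77 |
| 4 | 176 | 11 | 3.57 | 6.28 |
| 5 | 269 | 14 | 6.34 | 17.06 |
| 6 | 201 | 13 | 8.42 | 16.93 |
| 7 | 322 | 15 | 6.41 | 20.66 |
| 8 | 149 | 4 | 3.87 | 5.76 |
| 9 | 345 | 19 | 4.65 | 16.04 |
| 10 | 152 | 7 | 5.03 | 7.64 |
| 11 | 198 | 23 | 8.28 | 16.39 |
| 12 | 136 | 11 | 4.57 | 6.21 |
| 13 | 173 | 5 | 3.67 | 6.34 |
| 14 | 281 | 10 | 3.16 | 8.88 |
| 15 | 331 | 49 | 7.52 | 24.89 |
| 16 | 353 | 2 | 2.63 | 9.28 |
| 17 | 147 | 2 | 3.01 | 4.43 |
| 18 | 135 | 4 | 2.00 | 2.70 |
| All | 4,283 | 224 | 4.71 | 201.92 |

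Excess = (224 - 201.92)/4,283 = 0.516 points. The Mantel-Haenszel risk difference is 0.515.

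| Method | Unmatched (J1) | Standardised to J2 |
|---|---|---|
| Miettinen-Nurminen | 0.006 to 1.34 | -0.11 to 1.22 |
| Wald | -0.03 to 1.30 | -0.14 to 1.17 |

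Observed/expected is 224/201.92 = 1.11 (exact Poisson 0.97 to 1.26). The shift is 0.634 - 0.516 = 0.118 points, about a third of the standard error (0.118/0.340 = 0.35).

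**5. Sensitivity.**
- *Centre 4.* Table C1 codes it as outside inner Paris, yet its community count is 426,453 over 34 days, or 12,543 per day at 3.57%. That resembles Paris; the other nine EDs outside inner Paris have 3,720 to 6,839 per day. Giving centre 4 the lowest rate in Table J2 (2.00%) makes the expected total 199.2 and the excess 0.58. The highest (8.42%) makes it 210.5 and 0.32. The stratified Miettinen-Nurminen interval includes zero at both ends (-0.05 to 1.29; -0.31 to 1.02).
- *Denominator.* The footnote to Table E1 reads "Patients with indeterminate results or a known positive SARS-CoV-2 status were not included in this table", and that table has 4,192 patients, 4,283 - 4,192 = 91 fewer than Table J1. With 4,192, the unmatched difference is 0.75 (Miettinen-Nurminen 0.11 to 1.47). The standardised one is about 0.63 (binomial -0.05 to 1.31), if the 91 are spread across centres in proportion.
- *Variation between EDs.* The intervals above treat patients as independent. One based on between-centre variation (t, 17 df) is -0.95 to 1.98.

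**The case against.** The strongest reply is that Tables J1 and J2 deliver what was planned, one overall and one per-ED comparison, and that section 2.2 names the region's rate as the comparator. Weighting by ED mix is then partly a different estimand, and only the mismatch in calendar time is a flaw. This stands in part. The effects of department and of time cannot be separated from the printed tables. But a regional rate for unspecified dates does not answer whether an ED finds more than community testing did in the same place and weeks.

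A second reply is that Table J2 is printed directly below, with a note that only three EDs were higher, so the variation is visible. That is fair, but no pooled estimate is drawn from it.

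Three stronger readings are tempting and go too far.
- A reader might infer that Table J1 covers the whole 15 weeks and that Table J2 is exactly time-matched. The daily counts are compatible with this, but no dates are given and Appendix J does not say how many departments Table J1 pools.
- A reader might infer that matching turned a clear finding into a null one. It did not. The Table J1 lower limit was 0.006, and whether its interval excluded zero already depended on the method.
- Without centre 15, observed and expected are 175 and 177.0. That shows the influence of one ED, not a mismatch of windows.

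The proposed estimate is also not fully like for like. In Table E1, 133 of 216 new diagnoses with symptom data reported symptoms. Among those without, (216 - 133)/(4,062 - 766) = 83/3,296 = 2.5% were positive, against 4.6% in the asymptomatic community pool. That gap is much larger than 0.12 points, and stratification by ED leaves it untouched.

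**Conclusion.** The concern holds as a modest one. Table J1's pool is not weighted to where and when the EDs screened. Standardised to the trial's own Table J2, the excess is 0.52 points (stratified Miettinen-Nurminen -0.11 to 1.22), or about 0.32 to 0.58 depending on centre 4. Higher ED positivity should not be concluded from Table J1. Equally, the interval allows an excess above one point, so the absence of a difference is not shown.

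The arithmetic rests on the printed Table J2 counts. Calling the result time-matched rests on the inference that those counts cover each ED's intervention period. If they do not, Table J1 is still not weighted to the EDs' departments, and the undefined windows are themselves the gap. The primary outcome is unaffected.

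**What to change.** - In Changes to the analysis plan, secondary endpoints, define the overall ED-versus-community comparison as stratified by ED. Each ED is compared with community tests in its own department over its own intervention dates, pooled as a stratified Miettinen-Nurminen or Mantel-Haenszel risk difference.
- State the start and end dates and the departments behind Tables J1 and J2, and check the department assigned to centre 4.
- Base the conclusion on the stratified estimate, keep the crude Table J1 figure beside it, and label the change post hoc.
- State that the ED group includes paucisymptomatic patients while the comparator is asymptomatic adults, and that stratification does not remove this difference.

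The cost is one SAP sentence, a re-analysis of data already tabulated and a check of dates. The downside is that the stated result becomes less favourable.
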